### Data collection

Data collection time points are outlined in Fig. 1. Study personnel will assess the subject’s pain score and vital signs at baseline and again at eight predetermined intervals using the 11-point NRS (Fig. 3). Adverse events will be monitored throughout the follow-up period. Additionally, subject satisfaction with their care and total amount of required analgesic medications will be assessed at the conclusion of the study for each participant. Baseline demographic characteristics and information on mechanism of injuries will also be gathered at the time of enrollment. As the population being evaluated will be followed-up for only 24 h at a single study site and will have substantial physical trauma, it is likely that losses to follow-up through discharge prior to 24 h or patients leaving against medical advice will be minimal.

### Data management

As the trial site will likely be in a setting lacking consistent access to electricity, data will be collected initially on preprinted standardized Data Collection Forms. Forms will be organized based on unique participant identification numbers and contain no personal identifiers. After collection, data will be entered into a password-protected database using REDCap electronic data capture tools by a member of the research team and backed up to an external encrypted hard drive daily [37]. All data will undergo subsequent re-entry after the acute response phase to evaluate for input errors. If a discrepancy between the first and second entry is found, the entry will be reconciled by consulting source documents. The original paper versions of all study documents will be securely stored and accessible only by study investigators.

### Statistical analysis

#### Sample size

The sample size for this study uses a framework of an equivalency trial with parenteral morphine as the standard of care versus morphine with RA as the novel treatment. The new modality is further divided into two arms of RA: FICB and US-guided FNB. For the purpose of this study, a clinically important effect size was defined as a 20 % change in the primary outcome of the SPID. Based on this assumption, a sample size of 63 patients per arm provides 90 % power to show equivalence between each group (e.g. RA administered via FICB as compared to standard care or RA performed using a FNB versus standard care), assuming a standard deviation (SD) up to 20, a difference between the SPID group means of 0 and an equivalence of 13, at a 2.5 % significance level (one-sided). Allowing for 10 % attrition, the sample size is 69 patients per arm, with 207 participants in total.

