## Methods

### Design

The RAPID study will be conducted in the aftermath of a major earthquake to which a Médecins Sans Frontières (MSF) field hospital is deployed at the request of the local Ministry of Health (MoH). The study design is a blinded RCT using an equivalence design. After obtaining informed consent, earthquake victims with serious lower extremity injuries will be randomized to one of three study arms. Eligible participants will be randomized in a 1:1:1 allocation ratio to either: standard care (defined below); standard care plus an anatomic landmark-guided FICB; or standard care plus an US-guided FNB. The structure of the study is illustrated in Fig. 1.

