### Aims

The goal of the RAPID study is to transform the way that serious injuries are managed after earthquakes and other disasters by introducing a cost-effective and anatomically appropriate method for pain control. The trial will enroll patients in the aftermath of a major earthquake to determine whether RA, either with or without US-guidance, can reduce suffering from lower limb injuries, as compared to current standard of care for pain control in these settings. The study will also evaluate if a brief, focused training for international and local generalist health care providers in RA is sufficient for them to gain competence in the RA procedures.

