#### Outcome analysis and reporting

The primary outcome variable, SPID, will be calculated using the pain-intensity difference (PID) at each time point outlined in Fig. 1, which is the difference between the patient’s pain level at that time on a standard 0–10 scale and the patient’s baseline pain level [25]. The SPID will be calculated by summing the pain intensity difference (PID) at each of the study time points, weighted by the amount of time since the prior assessment; this approximates the area under the curve for PID over time. SPID will also be reported as a percentage of maximum possible SPID.

Baseline patient characteristics and outcome measures will be reported using means and standard deviations, medians and ranges, or proportions as appropriate. Analysis of variance (ANOVA) and Student’s *t* test will be employed to determine differences between study arms for continuous measures, including the primary outcome of SPID, and the Fisher’s exact test will be used for differences in categorical variables. Two-way ANOVA testing with repeated measures in one factor (time) will be performed to compare the effect of treatment arm over time on pain-intensity measures.

Missing data will be handled using multiple-imputation models and standard error uncertainty estimates in which missing data will be replaced using summary outcomes from participants with complete data for each variable of interest. To assess the robustness of the models, sensitivity analyses will be performed in which the primary outcome will be compared with and without those lost to follow-up included and assumed to have the mean SPID correlating to the allocation arm of initial randomization.

Prior to trial initiation, a statistical analysis plan with formalized procedural protocols will be created. Analyses will be performed using STATA 13.0 (StataCorp LP, College Station, TX, USA). A *p* value of less than 0.05 will be considered significant for all analyses. All data analyses will be coded on program files to allow independent reproduction of analyses.

Reporting of outcomes will follow the most up-to-date Consolidated Standards of Reporting Trials (CONSORT) guidelines as well as the extensions to equivalence trials; and to nonpharmacological interventions. The collected data set will also be made available in conjunction with the associated trial report.

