## Discussion

Earthquakes cause the greatest burden of injuries among all natural disasters globally [1, 2]. Studies of injury patterns from earthquakes show that approximately half of all patients sustain lower extremity injuries [3–6], and that pain management for these victims is often inadequate [11–13]. The shortage of sufficient narcotic medications in LMIC settings, where the majority of earthquake injuries occur, further compounds this problem [16].

While there are reports on the use of RA for pain control in disaster settings, there have been no controlled studies evaluating whether RA has added benefit over narcotics alone [13, 29]. This trial will rigorously evaluate the role of RA and also be the first to assess if a focused training for generalist health care providers is sufficient to effectively perform RA in the aftermath of a major disaster. Given the novelty of this particular research study, as well as the approach of performing an RCT in the aftermath of a major disaster, the RAPID trial has the potential to transform the management of pain in earthquake settings as well as research in acute disaster settings.

The utility of RA in pain management of lower extremity trauma in high-income country hospitals is well-described [24–26]. However, the injury patterns and clinical parameters of this population are not representative of a post-earthquake setting, where resources are often scarce and injuries more complex. Although there are anecdotal reports on the use of RA from contemporary earthquake events [13, 28, 29], this data is limited and equipoise exists as to whether RA improves pain control for lower extremity injuries of disaster victims. The RAPID study will utilize a blinded RCT equivalence design to address this patient-centered question. Although a nonrandomized observational study would be less resource and methodologically intensive, such a design would likely suffer from confounding as patients with more serious injuries, who are more likely to experience adverse events and less likely to achieve adequate pain control, would have a higher probability of receiving RA. Additionally, as the RAPID study outcomes include assessments of pain, blinding is crucial in order to avoid bias due to the placebo effect and, therefore, necessitates a controlled trial design.

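### The 90 % power is for showing each regional anesthesia arm equivalent to morphine alone, but the aim and the named tests are about a difference

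*Protocol article*

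**What the plan says.** All references are to the protocol article.

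- **Design:** "The study design is a blinded RCT using an equivalence design". The Abstract uses the same label, and the Discussion repeats it: "The RAPID study will utilize a blinded RCT equivalence design to address this patient-centered question". Both active arms are standard care plus a block.
- **Aims:** the trial asks whether RA "can reduce suffering from lower limb injuries, as compared to current standard of care for pain control in these settings". The Background says the same. The Discussion describes the evidence gap as "no controlled studies evaluating whether RA has added benefit over narcotics alone".
- **Sample size:** "The sample size for this study uses a framework of an equivalency trial with parenteral morphine as the standard of care". On that basis 63 per arm gives 90 % power to show equivalence, assuming SD up to 20, "a difference between the SPID group means of 0 and an equivalence of 13", at one-sided 2.5 %. Both worked examples compare a block arm with standard care. A clinically important effect is defined as a 20 % change in SPID, and no control mean is given. Attrition of 10 % brings the size to 69 per arm, 207 in total.
- **Outcome analysis and reporting:** ANOVA and Student's t test "will be employed to determine differences between study arms for continuous measures, including the primary outcome of SPID", with p < 0.05 as the criterion for every analysis. The margin of 13 does not appear in this section. Equivalence appears there only in the choice of CONSORT extension.

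**The concern.** Whether a block added to morphine reduces pain more than morphine alone is a superiority question. An equivalence result against control would mean that the block makes no difference as large as 13 SPID units, which is the opposite of what the trial hopes to learn. The 90 % is the chance of reaching that result when the block has no effect at all. It is not the chance of detecting a benefit.

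Two things are at stake. A reader cannot tell from the article which result counts as success. And in a trial labelled equivalence, a non-significant t test could be reported as equivalence, although failing to find a difference does not show that the difference is small.

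**Working it through.** **Inputs (Sample size section).** n = 63 per arm, SD = 20, margin 13, true difference 0, one-sided alpha 0.025, power 90 %.

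**Step 1. Reproduce 63.** For two one-sided tests at a true difference of 0, the normal formula is

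n = 2 × [SD × (z(0.975) + z(0.95)) / margin]² = 2 × [20 × (1.960 + 1.645) / 13]² = 61.5, so 62.

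With the t distribution, power is 89.7 % at 62 and 90.3 % at 63, so 63 is the smallest size that reaches 90 %. Other formulas with the same inputs do not give 63:

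- one-sided non-inferiority at 2.5 %: 50
- two-sided 5 % superiority for a difference of 13: 50 (51 with the t test)
- two one-sided tests at alpha 0.05: 52

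The figure is thus a true equivalence calculation and not a superiority calculation under the wrong name. For attrition, 63 × 1.1 = 69.3, which agrees with the stated 69.

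**Step 2. The two decision rules.** The standard error of a difference is 20 × √(2/63) = 3.56. With the t quantile of 1.979 on 124 degrees of freedom, the 95 % half-width is 1.979 × 3.56 = 7.05. If the observed SD is 20:

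- equivalence is shown when the observed difference is smaller than 13 − 7.05 = 5.95 in absolute value
- the t test is significant when it exceeds 7.05

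**Step 3. Probability of each result by true benefit** (63 per arm, SD 20, t-based):

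| True difference in SPID | Equivalence within 13 shown | Two-sided 5 % t test significant |
|---|---|---|
| 0 | 90 % | 5 % |
| 5 | 60 % | 29 % |
| 8 | 29 % | 61 % |
| 10 | 13 % | 80 % |
| 13 | 2.5 % | 95 % |

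The two columns move in opposite directions. Under the true difference of 0 used for the sample size, the t test named in the analysis section is significant 5 % of the time, by type I error alone.

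**Step 4. Power restated as superiority.** The target difference is an assumption. The article gives 13 only as the equivalence margin. Its 20 % change would equal 13 only if the reference SPID were 13 / 0.20 = 65, which is not stated. Over a range of targets, with 63 per arm and SD 20:

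| Target difference | Two-sided alpha 0.05 | Alpha 0.027 (Dunnett-type, two comparisons with control) |
|---|---|---|
| 13 | 95 % | 92 % |
| 10 | 80 % | 71 % |
| 8 | 61 % | 50 % |
| 5 | 29 % | 21 % |

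By the normal approximation at alpha 0.05, the detectable difference is 11.6 units at 90 % power and 10.0 at 80 %.

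**The case against.** **The difference tests already match the aim.** This is true, and it narrows the fault. The tests fit the question; the design label, the meaning of the 90 % and the unused margin do not.

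**The promised statistical analysis plan could add an equivalence rule.** It could, and the absence of such a rule from an article is not the point. A later plan would still leave the article with a superiority aim and an equivalence power statement against control.

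**Equivalence may have been meant for FICB versus FNB.** The wording about equivalence between groups need not exclude that pair. However, both examples given are against standard care, so this reading does not remove the conflict.

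**Equivalence does not mean that the block is useless.** A reader might infer that the trial is powered to prove that RA adds nothing. The document does not support that. Equivalence within 13 excludes a benefit of 13 or more, not a smaller one. The article says SD up to 20. Below an SD of about 18.4 (6.5 / (1.979 × √(2/63))), a 95 % interval at 63 per arm can lie wholly within ±13 and still exclude 0.

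**Conclusion.** The point stands as a contradiction within the article between aim, power statement and named test. The 90 % is correctly calculated for equivalence to standard care, but it answers neither the trial's question nor the test it names. It drops from 90 % at no effect to 2.5 % at a benefit of 13.

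Two stronger inferences should be resisted. One is that the trial is too small: at 63 per arm, superiority power is about 95 % for a difference of 13. The other is that 95 % can simply replace 90 %. That figure depends on SD 20 and on 13 being the target, and the article does not link 13 to its 20 % change. At a target of 8, power would be 61 %, or 50 % adjusted. The error concerns the hypothesis, the meaning of the power and how the result will be read. It should be corrected before the trial starts.

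**What to change.** 1. State the primary hypotheses as superiority of FICB over control and of FNB over control on SPID, two-sided, and say how the two comparisons are handled.
2. Keep 63 per arm (69 with attrition). Replace the power statement with one for a target difference that the sponsor specifies and ties to the 20 % change, giving the control SPID assumed.
3. Correct the equivalence wording in the Abstract, Design, Sample size, Outcome analysis and reporting (the CONSORT extension) and Discussion.
4. If equivalence is wanted, keep it only for FICB versus FNB. Use a rule that the confidence interval must lie within a margin, and justify that margin separately. Do not carry over ±13 and its 90 % by default: if 13 were the whole benefit sought over control, that margin would accept a difference between techniques almost as large as the benefit itself. A tighter margin is costly. With 6.5, purely as an illustration, the normal formula gives 2 × [20 × 3.605 / 6.5]² ≈ 246 per arm, and 63 per arm would have under 1 % power.

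The cost is a protocol amendment with ethics notification, since ethical approval has been granted, made before the trial starts. The restatement itself needs no extra patients or data.

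### The SD of 20 and margin of 13 behind the stated 90 % power have no scale; read as NRS-hours, they give 90 % power only if the SD of the time-averaged pain change is about 0.83 point or less

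*Protocol article*

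**What the plan says.** The Sample size section adopts an equivalence framework: "The sample size for this study uses a framework of an equivalency trial with parenteral morphine as the standard of care". The size of effect that matters is given as a percentage: "a clinically important effect size was defined as a 20 % change in the primary outcome of the SPID". No mean is given for that percentage to refer to. The power statement is "a sample size of 63 patients per arm provides 90 % power to show equivalence between each group", at a one-sided level of 2.5 %, with the inputs "assuming a standard deviation (SD) up to 20, a difference between the SPID group means of 0 and an equivalence of 13". Neither the 20 nor the 13 carries a unit. After a 10 % allowance for attrition, "the sample size is 69 patients per arm, with 207 participants in total".

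The Outcome measures and Outcome analysis and reporting sections define the outcome to which these figures apply. At each time point over 24 h, the pain intensity difference (PID) is the current score minus baseline on a 0–10 scale. The SPID sums these differences, "weighted by the amount of time since the prior assessment; this approximates the area under the curve for PID over time". The time unit of the weights is not stated. The analysis section adds that SPID will be reported as a percentage of the maximum possible SPID as well.

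**The concern.** A power statement can be read only if its SD and margin are on the scale of the outcome being tested. Here two scales are in play: the time-weighted SPID that defines the primary outcome, and a percent-of-maximum version reported alongside it. The sample size text ties its inputs to neither.

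The choice matters. On a 24-h SPID in NRS-hours, an SD of 20 means that patients' average pain change over the day varies with an SD below one point on an 11-point scale. The eligibility criteria set no minimum pain score, and the plan expects mixed and complex injuries, so a larger SD is easy to imagine. If it is larger and the margin stays at 13, the trial could end without being able to declare equivalence for lack of precision alone. On the percentage scale the same two numbers describe a less demanding design.

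**Working it through.** **Inputs, all from Sample size:** SD 20, true difference 0, margin 13, one-sided alpha 0.025, power 0.90, attrition 10 %. From the outcome sections: 0–10 scale, 24 h of follow-up, time-weighted sum.

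**1. The plan's own figure.** For two one-sided tests with a true difference of 0:

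n per arm = 2 × [SD × (z(0.975) + z(0.95)) / margin]²
= 2 × [20 × (1.960 + 1.645) / 13]²
= 2 × 5.546² = 61.5, so 62 by the normal approximation.

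With the t distribution, power is 89.7 % at 62 per arm and 90.3 % at 63. The stated 63 is therefore reproduced. A non-inferiority or superiority formula gives 50 per arm, and a one-sided 5 % level gives 52; neither matches.

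**2. The inputs in NRS-hours.** The largest possible SPID is 10 × 24 = 240. Dividing by 24 h gives the time-averaged change in NRS points:

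- SD: 20/24 = 0.83 point
- margin: 13/24 = 0.54 point

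**3. Sensitivity on that scale.** The protocol article gives no SD for pain, so the SDs below the first row are assumptions. The margin is held at 13. Power is t-based; the last column uses the formula in step 1.

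| SD of 24-h mean change (points) | SD of SPID (NRS-hours) | Power at 63 per arm | n per arm for 90 % |
|---|---|---|---|
| 0.83 (plan) | 20 | 90.3 % | 62 |
| 1.0 | 24 | 71 % | 89 |
| 1.25 | 30 | 35 % | 139 |
| 1.5 | 36 | 6 % | 200 |
| 2.0 | 48 | about 0 % | 355 |

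Power reaches 80 % at a SPID SD of 22.3, and 22.3/24 = 0.93 point.

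**4. The inputs as percent of maximum SPID.** Maximum SPID depends on baseline pain, which the article does not give.

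- Assumed baseline 7: maximum 7 × 24 = 168 NRS-hours. SD 20 % = 33.6 (1.4 points); margin 13 % = 21.8 (0.91 point).
- Assumed baseline 10: maximum 240. SD 20 % = 48 (2.0 points); margin 13 % = 31.2 (1.3 points).

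The ratio of margin to SD is unchanged, so power on this scale remains 90.3 % if the SD is indeed 20 percentage points.

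**5. Does the 20 % change settle the scale?** If 13 is the 20 % change, the mean SPID is 13/0.20 = 65. In NRS-hours that is an average reduction of 65/24 = 2.7 points; on the other scale it is 65 % of maximum. Both are possible, so the link does not identify the unit.

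**6. Attrition.** To keep 63 evaluable after a 10 % loss: 63/0.9 = 70 per arm, 210 in total. The stated 69 appears to be 63 × 1.1 = 69.3, rounded down. With 69 enrolled, 69 × 0.9 = 62.1 remain, and power at 62 is 89.7 %. The loss that 69 tolerates is 6/69 = 8.7 %.

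**The case against.** The strongest reply is that nothing has been miscalculated: the stated inputs give 63 per arm. That stands in full for the 63. The main point concerns an unstated scale, not a wrong sum.

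The second reply is that the percent-of-maximum scale appears in the plan, the important effect is itself expressed as a percentage, and on that scale 90 % can stand. This also holds as a possible reading. It does not dispose of the point, because the plan introduces that scale as an addition to the primary SPID. If the power was computed on it, the text should name it as the scale of the primary comparison.

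Third, a journal article condenses a fuller protocol, and a statistical analysis plan was to follow. That fairly excuses leaving out where the SD came from. It does not cover the unit of figures that the article itself offers as the basis of its power.

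A reader might go further and infer that the 90 % is very unlikely to be true, or that the equivalence test cannot succeed. The documents do not support either. They give no SD of pain and no time unit, so both inferences need an assumed SD and the NRS-hours reading. Even then power declines by degrees: 71 % at 1.0 point, and near zero only at about 2.0.

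On attrition, the effect is small (89.7 % against 90.3 %), and the Data collection section expects few losses.

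**Conclusion.** The point holds in conditional form. The 90 % power is tied to no scale of the primary outcome. If the inputs are in NRS-hours over 24 h, that power requires an SD of about 0.83 NRS point or less for the time-averaged change, and it drops below 80 % above about 0.93 point with the margin held at 13. If they are percent of maximum SPID, the 90 % can stand, but on a scale that the plan does not name for the primary comparison. Either way the paragraph needs correcting. Which reading is right, and how large the true SD is, cannot be determined from the article.

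The attrition figure is wrong as written for a 10 % loss, whichever scale applies. It is a minor point.

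**What to change.** In the Sample size section:

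- State the scale of the 20 and the 13, and the observation window they refer to.
- State the mean SPID behind the 20 % change, and say whether 13 is that change.
- Put both inputs on the scale used for the primary analysis. If that is percent of maximum SPID, name it as the scale of the primary comparison in the outcome sections too.
- Replace the single 90 % with power over a range of SDs on that scale.
- Change 69 and 207 to 70 and 210, or keep them and give the tolerated loss as about 8.7 %.

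The cost is one rewritten paragraph and, if the attrition figure is corrected upwards, three more patients. Clarifying the scale does not itself add patients. If the scale proves to be NRS-hours, however, the restated power may be less favourable, and rewording cannot restore it. The sponsor would then have to weigh the table's larger sample sizes against accepting lower power.
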